### Intervention group

General practitioners of the intervention group participate in a modern education on strategies of structured hypertension management in primary care. It is conducted as an in-class, three-session medical education program. Central elements of the education are 1) training on valid upper arm blood pressure readings; 2) evidence-based information on resistant hypertension, secondary hypertension, and modern pharmacotherapy, in the form of presentations and group discussions of actual cases; and 3) the introduction and distribution of practice tools to facilitate the long-term implementation of hypertension management. The following practice redesign tools are provided in print and electronic versions:current hypertension guidelines [7],10-step checklist how to obtain standardized upper arm office blood pressure readings according to guidelines [7],template of a blood pressure documentation sheet for serial documentation of blood pressure values by patients,list of electronic blood pressure devices that carry the quality seal of the German Hypertension League,prescription template detailing how to prescribe an electronic blood pressure device,prescription template detailing how to prescribe relaxation training programs (progressive muscle relaxation and autogenous training),checklists to assist in the diagnosis of secondary hypertension,templates for specialist referral sheets for the work-up of secondary hypertension,overview sheet specifying the mechanism of action of the various antihypertensives,information sheets on blood pressure lowering effects (in mmHg) of different single and combined blood pressure lowering measures such as regular physical activity or intensified pharmacotherapy [3], andpatient information leaflet about hypertension.

All information sheets are written in an easily understandable language and designed in a clear layout so that they can be used for patient information and education. General practitioners and practice assistants participate in the session on blood pressure measurements, while all other sessions are offered to physicians only. The education sessions are supported by hypertension specialists from the German Hypertension League.

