### Control group

General practitioners of the control group are offered the same education sessions, but only after completing the follow-up data collection in both study arms. Control group patients receive treatment as usual.

Despite this sequential design, it cannot be excluded that study participation, 24-hour blood pressure measurement at baseline and follow-up, and completing a questionnaire at baseline and follow-up might influence the physicians’ and patients’ awareness for hypertension in both study arms.

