### Statistical hypotheses, methods, and analyses

The primary endpoint (differences in the blood pressure control rate between intervention and control group) will be analyzed using a chi-square test. A *P* value <0.05 will be considered significant.

For analyses of secondary endpoints, average blood pressure levels at baseline and at follow-up will be determined for all study patients and separately for patients of both study arms. Differences between baseline and follow-up will be tested for significance within each study arm using paired t-tests. Differences in the mean systolic and diastolic blood pressure level of patients of the intervention group and patients of the control group will be tested for significance using an adjusted t-test for independent samples, which accounts for the intra-cluster correlation [6].

The analysis will determine which elements of hypertension management have been implemented into everyday routine during the study period and which of them are regarded as being helpful. To describe the effect of single hypertension management strategies on blood pressure, bivariate analyses will be conducted.

A generalized linear mixed model will be performed to identify predictors on blood pressure control at follow-up. The model will include patient level covariates such as age, sex, lifestyle, comorbidities, and changes in each patient’s hypertension management as well as cluster-level covariates such as changes of hypertension-related diagnostic and therapeutic strategies. Modeling will account for cluster effects by random effects modeling. Statistical analyses will be performed using IBM SPSS Statistics for Windows, Version 22.0 (Armonk, New York: IBM Corp.).

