## Discussion

Studies have identified various barriers for hypertension control in regular care that are structured in physician-, patient-, health care delivery and health care system-related factors [12]. Our cluster randomized trial is based on results from randomized controlled trials that show that complex interventions combining physician education, intensified pharmacotherapy and patient recall systems were most effective in improving hypertension control [3] and even decreased 5-year all-cause mortality [4]. Our intervention is using physician and practice assistant in-class education as the primary intervention, aiming at long-term hypertension control by modifying practice organization and patient education. Therefore, various hypertension management strategies for practice redesign are offered to physicians (so called ‘practice tools’) [13,14].

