Interventions aimed at changing regular care need to be based on an in-depth understanding of the health care system that they are addressing [13]. We designed our intervention for the German primary care system, which is based mainly on one- or two- (rarely more) physician private practices that self-organize patient care and are regionally distributed in the various neighborhoods close to their patients. These practices typically serve sickness fund and privately insured patients likewise; therefore, they follow the regulations of the various insurance systems parallel. While all physicians and practice assistants in the intervention group will participate in the educational intervention to familiarize them with the array of options of a practice hypertension management, the practices remain free with regard to their choice of diagnostic, therapeutic and practice redesign strategies. Thereby, we follow a core principle of practice redesign that assumes that practice teams know best about their practice-specific contextual factors such as, for example, practice structures or organization [13]. Practitioners are more likely to pursue self-selected strategies than a fixed set of approaches.

Methodologically, we will address this expected inter-cluster variance by three strategies. First, for each practice we will obtain the hypertension management strategies at baseline and follow-up: this will allow us to assess which strategies are newly tried. In addition, the practices will be asked which strategies they will continue to use for their hypertension management. Second, based on this information we will outline typical patterns of hypertension management for inter-cluster analyses. Third, for each patient we will obtain the information in which changes in diagnostic, therapeutic and educational interventions occurred between baseline and follow-up. Depending on the frequencies and potential effects on hypertension control in bivariate analyses, we will include an appropriate selection of single measures or patterns of redesign aspects in the final regression model to describe the effects of the relevant hypertension management strategies on hypertension control in primary care patients.

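### The bivariate analyses of single management strategies leave out study arm, so a tool with no effect of its own can be credited with part of the programme's effect

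*Protocol article*

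**What the plan says.** Under Statistical hypotheses, methods, and analyses, the protocol article plans the following: "To describe the effect of single hypertension management strategies on blood pressure, bivariate analyses will be conducted". It mentions no restriction to one arm, no stratification and no arm term. The mixed model for control at follow-up, in the same section, gives examples of patient-level and practice-level covariates, including changes in strategies. Study arm is not among the examples.

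The Discussion says how the bivariate results will be used: "Depending on the frequencies and potential effects on hypertension control in bivariate analyses, we will include an appropriate selection of single measures or patterns". What is selected goes into the last regression, whose purpose is to show what the relevant strategies do to hypertension control.

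On who has the tools, the Intervention group section lists among the central elements of the education "the introduction and distribution of practice tools to facilitate the long-term implementation of hypertension management". The Control group section says that control practitioners "are offered the same education sessions, but only after completing the follow-up data collection in both study arms". The Discussion links strategies and tools: "various hypertension management strategies for practice redesign are offered to physicians", with the term practice tools given in brackets.

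Stratification by arm does appear under Outcome measures, but for the endpoint on changed practice management. It is not stated for the relation between strategies and blood pressure.

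**The concern.** A bivariate analysis has two variables, here strategy use and blood pressure. Pooled over all 24 practices, users of a study tool come mainly from the intervention arm, while non-users include most of the control arm. The comparison then carries part of the arm contrast under the tool's name. Benefit from the measurement training, the pharmacotherapy teaching or a different tool is credited to whichever tool is being examined.

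This is separate from clustering and from self-selected uptake. It remains with a cluster-valid test, and it remains if practices pick tools at random. A random practice effect does not remove it either, because arm is a fixed difference between practices.

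What is at stake is the trial's account of which programme elements help. The direction of the error is known: if the programme works and a tool is used more in the intervention arm, the tool looks better than it is. Because the bivariate results steer model selection, the error can carry into the final model.

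**Working it through.** The article gives no figure for the strategy analyses, so there is none to reproduce.

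**Inputs from the article**
- 24 practices in two equal arms, so 12 each (Practice and patient recruitment).
- 169 patients, 101 of them in the intervention arm, so 68 controls (Inclusion and exclusion criteria for patients).
- Control rates of 35% and 70%, and intraclass correlation 0.05 (Sample size calculation).

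**Assumed, not in the article:** the proportion of practices using a tool, q1 in the intervention arm and q0 in the control arm. The tool has no effect, and uptake within each arm is random.

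**Formula.** For such a tool:

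apparent difference = arm effect × [P(intervention | user) − P(intervention | non-user)]

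The bracket is the inherited share.

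**Worked example, q1 = 50%, q0 = 0.** All users are intervention patients, so the first term is 1. Non-users are 50.5 intervention and 68 control patients, so the second term is 50.5/118.5 = 0.426. The share is 0.574, and 0.574 × 35 = 20.1 points.

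**Worked example, q1 = 75%, q0 = 25%.** Users are 75.75 and 17, giving 75.75/92.75 = 0.817. Non-users are 25.25 and 51, giving 25.25/76.25 = 0.331. The share is 0.486, and 0.486 × 35 = 17.0 points.

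| q1 / q0 | Share inherited | Points at 35% v 70% | Points at 35% v 50% |
|---|---|---|---|
| 25% / 0% | 47% | 16.6 | 7.1 |
| 50% / 0% | 57% | 20.1 | 8.6 |
| 75% / 0% | 73% | 25.5 | 10.9 |
| 100% / 0% | 100% | 35.0 | 15.0 |
| 50% / 25% | 25% | 8.8 | 3.8 |
| 75% / 25% | 49% | 17.0 | 7.3 |
| 50% / 50% | 0% | 0 | 0 |

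The same share applies to mean blood pressure. The Discussion cites systolic differences of −4.76 and −1.75 mmHg from two practice-redesign trials. With an arm effect of that size, shares of 57-73% give an inert tool about −2.7 to −3.5 mmHg or −1.0 to −1.3 mmHg.

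**Simulation check.** 4,000 runs per scenario, 12 practices per arm, 101 and 68 patients, beta-binomial outcomes with intraclass correlation 0.05, 35% v 70%. The entries are the percentage of runs in which the inert tool is significant at 5%.

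| q1 / q0 | Chi-square on patients, no arm | t-test on practice rates, no arm | Practice-level regression with arm |
|---|---|---|---|
| 50% / 0% | 67% | 46% | 2.7% |
| 75% / 0% | 89% | 80% | 3.3% |
| 75% / 25% | 60% | 31% | 5.3% |
| 50% / 25% | 22% | 6% | 4.3% |
| 50% / 50% | 7% | 1% | 4.8% |

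With no arm effect (35% in both arms), the apparent difference averages zero. The chi-square still rejects in about 9-10% of runs, which reflects ignored clustering and not this point. At 35% v 50%, the t-test on practice rates rejects in 14%, 23%, 12% and 5% for the first four rows. With arm included, the tool's estimated effect lies between −0.4 and +0.3 points and rejection between 2.7% and 5.6% in every scenario run.

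**The case against.** The analysis concerns strategies, which are not said to be limited to the handouts. The Discussion records them in every practice at baseline and follow-up, and records changes for every patient. Control practices can make such changes under usual care, and the Control group section concedes that taking part may raise awareness in both arms. Some tools, such as the guidelines, may already be in control practices. Uptake is nowhere stated and practices choose freely. The text speaks of describing, fixes no significance test and does not forbid analysis by arm. The mixed-model covariates are given only as examples, and an article may leave such detail to a fuller plan.

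Much of this stands, and it limits the size of the point. A reader might infer that an inert tool takes on the whole arm effect, or that tool use is nearly a stand-in for arm. The documents do not support either: the first needs use by every intervention practice and no control practice, and nothing establishes how closely use follows arm. A reader might also infer that each tool is to be formally tested. The text does not say so, and the rejection rates above only illustrate what would happen if it were.

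The objection does not remove the point. The method is stated, not merely left open, and as stated it has no place for arm. The purpose given is to describe an effect, and the Discussion acts on the result. The programme also exists to make uptake differ between arms.

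**Conclusion.** The point holds in a limited form. As written, the strategy analyses omit arm, and a tool with no effect can inherit part of the programme's effect: roughly a quarter to three quarters over the partial-uptake scenarios in the first table with unequal uptake. This requires that uptake differ by arm and that the programme work. If either fails, the spurious difference is zero. The size in points also depends on the arm effect, and the planned 35 points is the largest considered here. Strategies already common in usual care are less affected. The analyses are exploratory, and neither the primary endpoint nor the between-arm comparison of mean blood pressure is touched. It is a cheap improvement that should be made before conclusions are drawn about single programme elements.

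**What to change.** In Statistical hypotheses, methods, and analyses, replace the unqualified bivariate analyses with analyses of strategy use against follow-up blood pressure within the intervention arm, or with arm always included, and account for clustering by practice in either case. Name study arm as a fixed covariate in any mixed model that contains strategy terms, and apply the same rule to the screening step in the Discussion. Report the results as associations: adjusting for arm removes the inherited arm contrast, but uptake remains the practices' own choice.

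This takes one or two sentences and no new data. The cost is precision, because the within-arm comparison rests on 12 practices and 101 patients. For a tool that no control practice uses, including arm does not avoid this loss, since the information on the tool then comes from the intervention arm alone.

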### Sample size calculation

For the primary endpoint, a blood pressure control rate of 35% is assumed for the control group, while a blood pressure control rate of 70% is assumed for the intervention group [8,9]. Assuming an equal number of clusters per study arm, an average cluster size of five patients and an intraclass correlation coefficient of 0.05 [5], ten clusters per study arm are needed to detect the assumed effect using a chi-square test with a two-sided significance level of 5% and a power of 80%. Sample size calculation was performed in R package CRTSize, function n4props [10].

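### Self-selected, post-randomisation changes in care are screened by bivariate results and then read as effects on blood pressure control; they should be reported as baseline-adjusted associations, apart from any adjusted estimate of the intervention effect

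*Protocol article*

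**What the plan says.** Three statements in the protocol article work together.

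- **Bivariate step** (Statistical hypotheses, methods, and analyses): "To describe the effect of single hypertension management strategies on blood pressure, bivariate analyses will be conducted". No adjustment is mentioned, and random effects are mentioned only for the later mixed model.
- **Mixed model** (same section): its aim is to find predictors of control at follow-up. Besides patient characteristics and changes in each patient's management, it takes "cluster-level covariates such as changes of hypertension-related diagnostic and therapeutic strategies". Practice enters as a random effect.
- **Selection and reading** (Discussion): "Depending on the frequencies and potential effects on hypertension control in bivariate analyses, we will include an appropriate selection of single measures". Grouped strategies may be entered in place of single ones. Whatever is selected is then used "in the final regression model to describe the effects of the relevant hypertension management strategies on hypertension control in primary care patients". The same paragraph places the changes between baseline and follow-up.

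The Intervention group section and the Discussion leave practices free to choose their diagnostic, therapeutic and redesign strategies. The Abstract says the programme aims to change physician awareness and practice design. The intervention is tested elsewhere in the plan: control rate by a between-arm chi-square test, and mean pressure by a t-test that allows for intra-cluster correlation.

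**The concern.** Only the offer of education is randomised. Whether a given patient's care then changes is decided by the practitioner, who knows the patient's pressure. If care is changed more readily where pressure is high, patients with a change start from a worse position. A crude comparison then mixes the effect of the change with the reason for making it. A helpful strategy can look useless or harmful, and the bivariate result also influences whether it enters the final model. The protocol uses causal wording for both steps, and the Discussion makes the strategy effects a main aim of the final regression.

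The second issue is conditional. Changes in care are how the education is meant to work. A model that holds them fixed does not give the total effect of being allocated to education. This matters because this is the only analysis of control that uses covariates, and the only one said to account for clustering. The Outcome measures section says patient characteristics are collected to control for confounding. Anyone wanting an adjusted or clustered answer on the primary endpoint is likely to turn to this model.

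**Working it through.** The plan gives no figure for this model. The checks below use its assumed control rates and otherwise assumed inputs.

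**1. Confounding by indication in the bivariate step**

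Inputs from the documents: control means 24-hour pressure below 130/80 mmHg (Outcome measures), of which only the systolic limit is used here. Assumed inputs: systolic SD 11 mmHg at both times; correlation 0.6 between baseline and follow-up; mean systolic pressure 135, 138 or 140 mmHg before any change in care; true effect of the change −4 mmHg; probability of a change rising with baseline pressure, with logistic slope 0.05, 0.10 or 0.15 per mmHg. Simulation of 400,000 patients without cluster effects.

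| Selection slope per mmHg | Crude odds ratio for control | Adjusted for baseline pressure |
|---|---|---|
| 0.05 | about 1.10 | about 2.2 |
| 0.10 | about 0.76 | about 2.2 |
| 0.15 | about 0.59 | about 2.2 |

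A repeat run over the three means gave adjusted values from 2.12 to 2.27. With no selection (slope 0) the crude odds ratio was 1.80 to 1.88. The gap from there to 2.2 reflects the odds ratio changing when a strong predictor is added. The fall from about 1.8 to 0.59 is confounding.

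The point of reversal follows by hand on the mmHg scale. With equal SDs the follow-up slope on baseline is 0.6, so

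crude difference = −4 + 0.6 × (baseline difference between patients with and without the change).

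This is zero at 4 / 0.6 = 6.7 mmHg. A larger baseline gap makes a helpful change look harmful.

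**2. What the arm term would mean if arm were entered**

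Inputs from the documents: "a blood pressure control rate of 35% is assumed for the control group" and "a blood pressure control rate of 70% is assumed for the intervention group" (Sample size calculation). The odds ratio is (0.70/0.30) / (0.35/0.65) = 4.33. Assumed: the education acts only through one measured change in care, made in 20% of control and 90% of intervention patients. Control probabilities of 25% without the change and 75% with it reproduce the planned rates:

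- control arm: 0.80 × 0.25 + 0.20 × 0.75 = 0.35
- intervention arm: 0.10 × 0.25 + 0.90 × 0.75 = 0.70

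Given the change, control is 75% in both arms; without it, 25% in both. The adjusted arm odds ratio is therefore 1.0, against 4.33 unadjusted. Simulations with uptake of 10–20% versus 80–90% gave 0.98 to 1.00.

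The shift need not be downward. When the change has no effect and unmeasured severity drives both the change and control, the change itself shows odds ratios of 0.66 and 0.49 under weaker and stronger severity. Adjusting for it moves the arm odds ratio up, from 4.09 to 4.68 and from 3.38 to 4.34. In none of these cases does the adjusted arm term reproduce the unadjusted between-arm comparison.

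**The case against.** The strongest reply is that the model does what it was set up to do. Its stated aim is predictors, not the test of the intervention. Changes in practice-specific management are a key secondary endpoint, and asking which strategies go with control requires post-randomisation variables. That stands: including such variables is not in itself an error. What does not follow is reading their coefficients, or crude comparisons, as effects.

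A reader might infer that the plan erases the intervention effect. The documents do not support this. Arm is not said to be in the model, the primary and cluster-adjusted tests contain no post-randomisation covariates, and the loss shown above assumes full mediation through a perfectly measured change.

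A reader might also infer that arm and baseline pressure are left out of the model. Both covariate lists are given as examples, and a condensed article may leave the full list elsewhere, so this cannot be determined. The crude reversal therefore describes the bivariate step. It carries into the mixed model only through term selection, or if baseline pressure is in fact omitted.

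Finally, a reader might count expected false positives across the eleven tools in the Intervention group section. No selection threshold is stated, and those handouts and templates are not shown to be the variables screened, so no such rate can be given.

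**Conclusion.** The concern holds in a limited form. As written, the protocol plans crude bivariate analyses of non-randomised, self-selected changes in care, uses them to help choose model terms, and calls the results effects. In the illustration the crude odds ratio for a truly helpful change runs from 1.10 down to 0.59, and baseline adjustment restores its direction. The size rests on assumed SD, correlation, effect and selection slopes. Full recovery is built in, because baseline pressure is the only confounder simulated; in practice other confounding may remain.

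The point about the arm term is conditional on arm being entered, or on the model being used as the adjusted intervention analysis. The primary chi-square test and the adjusted t-test are untouched. This is a fault in a secondary analysis and its wording, worth correcting because the strategy results are a declared aim and the correction is cheap.

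**What to change.** 1. For any adjusted estimate of the intervention effect on control, specify a mixed logistic model with study arm, baseline 24-hour blood pressure, a pre-specified list of baseline covariates and a random practice effect. Include no changes in care after randomisation.
2. Put patient- and practice-level management changes in a separate model labelled exploratory and adjusted for baseline 24-hour pressure.
3. Keep the random practice effect, and preferably baseline pressure, in the screening step as well.
4. Replace effect wording with association in the analysis section and the Discussion, and say that strategies were self-selected.

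The data needed are already planned: 24-hour pressure is measured in every study patient at baseline, and arm and practice are known. The Trial status section reports that data management is still under way, so the change can be recorded before the analysis. The cost is one extra model, some rewording and a weaker claim for the strategy results.
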